## Abstract

**Background:**

Over recent decades, multifaceted nurse-led care models have been developed to reduce unplanned hospital transfers from long-term care facilities (LTCFs). In Switzerland, the INTERCARE model has demonstrated effectiveness, with core components including deployment of nurses in expanded roles (INTERCARE nurses), evidence-based communication tools, and advance care planning. However, resource-intensive implementation strategies such as 1:1 support meetings for model implementers pose challenges for scale-up, underscoring the need for more scalable implementation support. The INTERSCALE study compares two modes of delivering implementation support—an individualized and a collective-oriented approach—testing the hypothesis that the latter achieves non-inferior fidelity to the INTERCARE model and comparable reductions in unplanned hospital transfers at the LTCF level. Secondary aims are to compare implementation (acceptability, feasibility), economic (costs, cost-effectiveness), clinical (unplanned transfers), and organizational (staff absences, turnover) outcomes.

**Methods:**

This non-inferiority, effectiveness–implementation hybrid type III trial uses a cluster-randomized controlled design, with LTCFs as the unit of randomization. Forty German-speaking LTCFs in Switzerland (≥20 long-term care beds; cantonal accreditation) will be randomized (1:1) after formal consent to either individualized or collective implementation support, without blinding of LTCFs or the research team. In the individualized arm (20 LTCFs), leadership receives 1:1 support meetings, and INTERCARE nurses receive 1:1 coaching, mirroring the original INTERCARE trial. In the collective arm (20 LTCFs), leadership support and INTERCARE nurse coaching are delivered in group formats involving several LTCFs/INTERCARE nurses together at two-monthly intervals. The primary outcome is LTCF-level fidelity to the INTERCARE core components, analyzed with a binomial generalized linear mixed model including a random LTCF effect. Non-inferiority of the collective mode will be concluded if the lower bound of its 95% confidence interval for fidelity is within 15% of the individualized mode. A 12-month cost-effectiveness analysis from a multi-stakeholder perspective (LTCFs and research group) will estimate the incremental cost-effectiveness ratio using differences in implementation costs and unplanned transfers between arms; secondary outcomes include unplanned transfers, staff turnover, and absences.

**Discussion:**

This type III hybrid cluster trial addresses a key scaling challenge in implementation science by testing less resource-intensive implementation strategies for disseminating an evidence-based care model across LTCFs in routine practice.

**Trial registration:**

Prospectively registered on June 25, 2024, at ClinicalTrials.gov nr. NCT06473051.

**Supplementary Information:**

The online version contains supplementary material available at 10.1186/s13012-026-01489-0.

Contributions to literature
INTERSCALE evaluates the scale-up of the nurse-led INTERCARE model, previously shown to reduce unplanned hospital transfers from long-term care facilities (LTCFs), by comparing two modes of delivering implementation support to LTCF leadership and nurses in expanded roles: individualized one-to-one support versus collaborative group-based support across multiple LTCFs.This study will deepen understanding of which implementation support strategies are effective for implementing and scaling evidence-based care models in LTCFs, with a focus on feasibility in routine practice.INTERSCALE systematically compares the costs and effects of two modes of delivering the same implementation strategies, enabling an assessment of the model’s cost-effectiveness for reducing unplanned hospital transfers at the organizational (LTCF) level.

## Background

Over the last two decades, nurse-led care models have been developed to reduce unplanned hospital transfers, achieving a reduction of 6.1% to 11.7% in unplanned transfers and 30% in overall transfers [1–3]. Given that between 19% and 67% of unplanned hospital transfers from long-term care facilities (LTCFs) may be avoidable) [4–7] and that such transfers increase residents’ risk of adverse events and overall health care costs [8, 9], nurse-led care models offer a promising approach to improving system-level care for older adults. These models typically position nurses in expanded roles as clinical leaders who coach and empower teams and support interdisciplinary decision-making regarding transfers. In multidisciplinary teams, these nurses may be advanced practice nurses (e.g., clinical nurse specialists) or registered nurses (RNs) with additional training, responsible for comprehensive geriatric assessments, root-cause analyses, benchmarking of hospital transfers and quality indicators, and advance care planning with residents and relatives [10].

Despite their promise, few evidence-based models that reduce unplanned transfers have been successfully scaled up. The EVERCARE model, which paired primary care physicians with nurse practitioners to reduce preventable hospital admissions in US LTCFs, proved less effective when implemented in the UK, partly due to poor information systems [11, 12], underscoring the importance of a careful contextual analysis before scale-up. Similarly, the MOQI model, which reduced hospitalizations in Missouri LTCFs by 30% [13], was successful in some facilities but not in others, possibly due to insufficient leadership engagement and support for local change [12]. Overall, there are limited examples of healthcare interventions that have been successfully taken to scale [14].

In Switzerland, the INTERCARE nurse-led care model was developed and demonstrated effectiveness in reducing unplanned hospital transfers in 11 LTCFs [15]. INTERCARE comprises six core components: 1) an INTERCARE nurse, a registered nurse with geriatric expertise in an expanded role who also acts as an implementer to introduce other components; 2) strengthened interprofessional collaboration; 3) advance care planning; 4) evidence-based communication tools (STOP&WATCH, ISBAR); 5) comprehensive geriatric assessment; and 6) data-driven quality improvement. Designed to drive organizational change, the model equips LTCF leadership and nurses in expanded roles with new skills and supports them to introduce and sustain new processes. In addition to reducing unplanned transfers, anecdotal evidence in the original study suggested possible organizational effects on staff turnover and absences. However, the impact of nurses in expanded roles on these outcomes remains largely unexplored [16]. INTERCARE showed high acceptability, fidelity, and sustainability, but required substantial time and financial investment in personnel resources from the research team to provide implementation support [15, 17–19].

### Implementation strategies of nurse-led models

LTCFs are complex organizations in which implementing innovations is challenging due to multilevel influences, continuous change, high staff turnover, resource constraints, top-down management, and communication problems [20]. To address these challenges, locally tailored and cost-effective implementation strategies are pivotal, where implementation strategies are understood as techniques that enhance the adoption, implementation, and sustainability of evidence-based interventions such as INTERCARE [21].

Existing studies on nurse-led care models in LTCFs report varied implementation strategies targeting both staff and leadership. From the perspective of the Interactive Systems Framework for Dissemination and Implementation (ISF), these strategies primarily focus on the delivery system level [22]. The ISF distinguishes three systems: the delivery system, which implements the innovation; the support system, which supports the delivery system in implementation; and the synthesis and translation system, which synthesizes research and prepares it for use by the other two systems. Common strategies to support LTCF staff include training, protocols, clinical benchmarking, champions, and new clinical teams. In contrast, leadership-level strategies are less frequent and mainly consist of clinical benchmarking and training (e.g., in quality improvement methods and good practices) [11, 23–29]. These strategies are often delivered by research teams or private companies, representing the ISF’s support system level. However, the most effective strategies for implementation and sustainment remain unclear, are highly context-dependent, and are often poorly distinguished, inconsistently reported, and entangled with intervention descriptions, hampering cross-study comparisons [30, 31]. Economic analyses are lacking, and few studies report on strategies during the sustainment phase.

During the INTERCARE study, LTCFs greatly valued the implementation support provided by the research team, particularly the bimonthly support meetings with leadership and the biweekly one-to-one coaching sessions for INTERCARE nurses—strategies rarely described in the literature. These meetings enabled teams to reflect on progress, address barriers, and co-develop solutions, and were perceived as key to successful implementation. However, because individualized meetings and coaching sessions were the most resource-intensive strategies for the research team, they limit scalability to additional LTCFs and, by extension, the model’s broader population impact. Therefore, more cost-efficient modes of delivering implementation support need to be examined, such as collaborative support meetings across multiple LTCFs and group-based coaching for INTERCARE nurses.

There is substantial evidence that group learning enables individuals to learn more effectively by engaging with peers and exchanging diverse perspectives. Social Cognitive Learning Theory (SCLT) posits that people learn by observing others’ actions and considering the consequences of those actions [32]. Because learning occurs through observation, modelling, and social interaction, SCLT emphasizes that learning often happens naturally in group settings where individuals can watch, imitate, and receive feedback from others [32]. Evidence from systematic reviews indicates that group and collaborative processes are critical facilitators of innovation implementation and improved outcomes in healthcare settings: McGuier et al. [33] identified effective communication and shared cognitive states as fundamental mechanisms through which teams collectively learn, coordinate, and implement new practices. Another review of implementation strategies in nursing practice showed that formal group learning methods and strategies leveraging social influence (e.g., opinion leaders) are statistically effective in changing practice [34]. Together, these findings suggest that collaborative learning approaches may strengthen implementation success.

To evaluate and compare implementation strategies, fidelity is a commonly used outcome, defined as the extent to which an intervention or procedure is delivered as intended [35]. Strategies that support effective implementation are expected to enhance adherence to core components; higher fidelity allows an intervention to exert its intended effect and is often associated with improved health outcomes [36]. Fidelity and sustainability – defined as the continued use of core components after implementation – are therefore key outcomes when comparing implementation strategies or, in this case, different modes of delivering implementation strategies when preparing a complex intervention for full-scale implementation.

### Scaling-up effective interventions

Scale-up has been defined as replicating and extending the reach of an intervention into other localities, cities, or regions [37], with the aim of achieving sustainable health benefits [37, 38]. Scale-up can be positioned at the pragmatic end of the explanatory-pragmatic continuum, focusing on moving real-world evidence into community and system-level practice [39]. Scaling up effective interventions enables additional settings and populations to benefit from practices proven successful in controlled research conditions and supports sustainable policy and program development [40].

However, several pitfalls in preparing for scale-up have been reported, including a lack of resources and contextual barriers, such as difficulties in adapting interventions to new settings [41]. Limited reporting and poor specification of implementation methods and strategies have further led to insufficient evidence to support scale-up, particularly when interventions and their implementation strategies are not described in sufficient detail to enable uptake and replication by government agencies, health care organizations, or foundations [42, 43]. This underscores the need for rigorously designed studies that both test scale-up and explicitly specify implementation strategies and their delivery.

Figure 1 illustrates how INTERSCALE fits into Barker and colleagues’ framework for scaling up health interventions [44], moving from an existing best-practice model to full scale. The process began with 1) building the INTERCARE nurse-led model based on existing international evidence and close engagement with early adopters and local stakeholders (set-up), and 2) testing the model in a first scalable unit of 11 LTCFs in the German-speaking part of Switzerland and developing a change package that includes both the context-sensitive complex intervention with six core components and the corresponding implementation strategies (develop scalable unit). It will continue with 3) validating INTERCARE in the INTERSCALE study in a test scale-up while evaluating cost-effective implementation strategies (test scale-up), and will eventually lead to 4) preparing for full-scale implementation [44].

**Fig. 1 Fig1:**
[figure not shown]
Different phases to reach full-scale implementation, adapted based on Barker and colleagues (2016) [44]

### The INTERSCALE study

The INTERSCALE study (Sustainable improvement of INTERprofessional care for better resident outcomes - SCAling up an Evidence-based care model for nursing homes) has two phases, each corresponding to a work package (WP). In WP1, the change package (i.e., the context-sensitive core components and corresponding implementation strategies) was developed, building on the existing material and insights from INTERCARE, which will then be tested in a second work package (WP2) (see Fig. 2). INTERSCALE thus constitutes a test scale-up of the INTERCARE model while simultaneously generating evidence on a more cost-effective mode of delivering implementation strategies (individualized vs. collaborative support meetings and coaching sessions at both LTCF leadership and INTERCARE nurse levels). This approach is intended to build toward full-scale implementation and address previously identified scalability challenges of INTERCARE for LTCFs.

**Fig. 2 Fig2:**
[figure not shown]
The INTERSCALE study

The central hypothesis is that replacing individual LTCF support with group-based support, and one-to-one INTERCARE nurse coaching with collaborative coaching, will reduce costs by minimizing the time investment of the support system (research team and external facilitators), while maintaining fidelity to the care model at LTCF level and preserving its clinical effect in reducing residents’ unplanned transfers.

The Exploration, Preparation, Implementation, Sustainment (EPIS) framework guides INTERSCALE [45]. WP1 corresponds to the preparation phase, in which minimal requirements of the core components were adapted and implementation strategies – along with the two delivery modes to be compared – were defined; WP2 covers the LTCFs’ preparatory, implementation, and sustainment phases.

Several methodological considerations informed the development of implementation strategies for WP2. Four workshops were conducted with LTCFs that had participated in INTERCARE and those interested in INTERSCALE. Using an implementation mapping approach [46], strategies were adapted to enhance adoption, implementation, and sustainability of the INTERCARE model. The minimal requirements for each core component were reviewed to focus on essential functions and distinguish these from the various ways components may be operationalized in practice [47], followed by adaptations using the FRAME method to align the model and strategies with the Swiss context [48]. In the first workshop, LTCFs identified barriers and facilitators and suggested adaptations. Performance objectives were then defined to address these barriers (see Supplementary Material 1), and the COM-B model and the Theoretical Domains Framework (TDF) were applied to identify behavioral determinants [49]. Finally, implementation strategies were adapted based on these determinants and described using the action, actor, context, target, time (AACTT) framework of Presseau and colleagues [50], resulting in a set of clearly specified strategies to be examined in the planned cluster-RCT (see Supplementary Material 2).

### Development of implementation strategies for INTERSCALE

For the planned cluster-RCT in WP2, two alternative modes of delivering implementation strategies were considered. To improve cost-effectiveness, the team initially explored removing strategies from INTERCARE or replacing them with less costly alternatives; however, workshop feedback indicated that LTCFs perceived all existing strategies as appropriate and necessary for successful implementation. Given that coaching of INTERCARE nurses and onsite support meetings with LTCF model implementers (i.e., local professionals responsible for implementing the model, including INTERCARE nurses) were the costliest strategies, shifting from individualized LTCF support and one-to-one coaching to collaborative formats was identified as the most feasible cost-saving approach. Limited expertise in external facilitation for long-term care, especially in organizational development, further supports concentrating expert resources in group sessions.

In addition, based on the WP1 workshops, two strategies were added to both study arms: 1) an implementation handbook describing INTERCARE’s core components, minimal requirements, performance objectives, barriers and facilitators, frequently asked questions, and resource materials; and 2) a workshop on data-driven quality improvement, as this core component had been poorly understood in the original study. A ticketing system was also introduced to streamline questions arising between support meetings by channeling email requests into a structured system, thereby changing the mode of delivery for continuous support compared with personal emails in INTERCARE. Figure 3 summarizes all implementation strategies across three phases of the EPIS framework, highlighting differences between the two arms in two strategies: facilitation and ongoing consultation.

**Fig. 3 Fig3:**
[figure not shown]
Implementation strategies per EPIS phase in work package 2

This protocol focuses on WP2, which includes the LTCFs’ preparatory, implementation, and sustainment phases, and will test the INTERCARE change package developed in WP1 to determine whether a shift from individualized to collaborative support can achieve similar implementation and clinical outcomes [15].

### Aims

The overall aim of INTERSCALE is to compare two modes of delivery for support and coaching (individualized vs. collaborative) to help LTCFs adopt and implement the INTERCARE model. This includes assessing implementation outcomes, calculating cost-effectiveness, and evaluating overall effectiveness. Specifically, the aims are:Primary outcome: To compare the individualized vs. collaborative arm in relation to LTCFs’ overall fidelity to the INTERCARE model (aim 1).Secondary implementation outcomes: To compare the two modes of delivery in relation to further implementation outcomes, i.e., LTCFs’ fidelity to the six single core components of the INTERCARE model, sustainability of the INTERCARE model, as well as the model’s acceptability and feasibility (secondary aim 2.1).Economic outcome: to assess the costs of the implementation strategies and to calculate the incremental cost-effectiveness ratio (ICER) of implementing the INTERCARE model in LTCFs. This will involve comparing the two modes of delivery from both the LTCFs' and the research team's perspectives, with the number of unplanned hospital transfers of LTC residents as the effectiveness outcome (secondary aim 2.2).Effectiveness outcomes:oTo assess the effect of the two modes of delivery on clinical effectiveness, specifically unplanned transfers of LTCF residents (secondary aim 2.3a).oTo assess the effect of the two modes of delivery on organizational outcomes, such as staff absences and staff turnover (aim 2.3b).

## Methods

### Study design

The trial follows CONSORT guidelines for cluster-randomized controlled trials (RCT) (Supplementary Material 3) [51]. This is a non-inferiority effectiveness–implementation hybrid type III cluster-RCT [52, 53], with LTCFs as the unit of randomization to reflect that the intervention targets organizational routines rather than individual residents (Fig. 4).

**Fig. 4 Fig4:**
[figure not shown]
Design for cluster-randomized controlled trial and data collection points

An explanatory mixed-methods process evaluation focusing on implementation strategies will accompany the trial but is not part of this protocol.

### Setting

The study takes place in the German-speaking part of Switzerland. In 2023, the Swiss Federal Office of Statistics reported 1,480 LTCFs with 100,727 beds, of which 1,117 LTCFs are in the German-speaking part [54]. Registered nurses account for about 30% of the skill mix in Swiss LTCFs, with most medical care provided by general practitioners (GPs); around 45% of LTCFs in the German-speaking part of Switzerland have a contract with a single physician, while about 90% work with several GPs (mean 16) [55, 56].

### Sample size and inclusion criteria

LTCFs will be recruited via LTC national and professional associations, magazines, direct contact, and snowballing. The sample size calculation assumes a 15% difference in overall fidelity between trial arms (65% vs. 80%). Based on a simulation with 2,000 iterations, a between-cluster variance of 0.1 (ICC = 0.029), and a two-sided alpha of 0.025, 18 LTCFs per arm provide 84% power to detect a 15% difference; for a 20% difference, power increases to 97%. Allowing for a 10% loss between consent and allocation, and after intervention start, the target sample is 40 LTCFs (20 per arm) (Fig. 5).

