### Data analysis

All quantitative data will be analyzed using R 4.5.x [70]. Descriptive statistics will summarize implementation, economic, and effectiveness outcomes and sample characteristics (means and standard deviations or medians and interquartile ranges for continuous variables, and frequencies and percentages for categorical variables). Multiple imputation will be considered depending on the extent of missing data [71]. Following CONSORT for cluster-RCTs [51], baseline differences between arms at the LTCF level will be presented using standardized mean differences and, where appropriate, frequencies and percentages.

For aim 1 (fidelity) and aim 2.1 (acceptability and feasibility), the non-inferiority margin is set at 15%. The non-inferiority of collaborative versus individualized support will be tested using binomial generalized linear mixed models with a random effect for LTCFs, and 95% confidence intervals; non-inferiority is confirmed if the lower confidence bound does not cross 15% below the arm II value.

A convergent mixed-methods approach will be used for aim 2.1. Qualitative data (interview notes, coaching activities reports, RAP sheets) will be analyzed using framework analysis [72, 73]. combining inductive and deductive themes to identify patterns in INTERCARE nurses’ practices and coaching approaches in acute situations. Qualitative findings will be compared with quantitative fidelity trajectories to explore fidelity moderators, and observational data will be coded in MAXQDA (https://www.maxqda.com/).

For aim 2.2, descriptive analyses will summarize intervention, implementation, and hospitalization costs by arm. A cost-effectiveness analysis will estimate the ICER, defined as the difference in costs between the two modes of delivery divided by the difference in their effects, measured as the number of unplanned hospital transfers. CEA helps identify ways to redirect resources to more cost-effective approaches [74]. We will use a multi-stakeholder perspective (i.e., LTCF and research group perspectives) and a 12-month time horizon, respecting the NICE guideline while reflecting data availability [75]. One-way sensitivity analysis and scenario analysis will be used to gauge our predictions’ level of uncertainty.

For aims 2.3a and 2.3b, the effects of the two delivery modes on unplanned transfers and staff outcomes will be analyzed using mixed-effects models analogous to those for aim 2.1, accounting for clustering at LTCF level.

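### The stated 84% and 97% power read as power to detect a difference at two-sided alpha 0.025, which is not the planned non-inferiority test (15% margin, 95% confidence interval)

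*Protocol article*

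**What the plan says.** Protocol article, Sample size and inclusion criteria: "The sample size calculation assumes a 15% difference in overall fidelity between trial arms (65% vs. 80" per cent). The section describes a simulation with 2,000 iterations, a between-cluster variance of 0.1 (ICC 0.029) and "a two-sided alpha of 0.025". It concludes that "18 LTCFs per arm provide 84% power to detect a 15% difference; for a 20% difference, power increases to 97" per cent. A 10% loss takes 18 facilities per arm to 20, or 40 in total. The section mentions neither a margin nor a true difference at which non-inferiority is to be shown, and it does not say which arm has 65%.

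Protocol article, Data analysis: for overall fidelity "the non-inferiority margin is set at 15" per cent. The test uses a binomial mixed model with a random facility effect and 95% confidence intervals. The Abstract gives the same kind of rule: the collective mode is non-inferior if its lower 95% limit is within 15% of the individualized mode. Study design also calls the trial a non-inferiority trial.

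**The concern.** The power statement and the decision rule do not describe the same test, in two respects.

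- **Hypothesis.** The assumed difference equals the margin, and power is said to rise when the difference grows to 20 points. That is how a difference test behaves. Non-inferiority power falls as the new mode gets worse: it equals the error rate at a 15-point deficit and is almost nil at 20 points. If the collaborative arm is instead the one at 80%, the scenario is that it is better, which is not the stated hypothesis of maintained fidelity.
- **Alpha.** Two-sided 0.025 puts 0.0125 in each tail and corresponds to a 97.5% interval. The decision uses a 95% interval, with 0.025 in the lower tail if it is two-sided.

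The 84% figure is the stated basis for the sample size. A reader cannot tell from it how likely the trial is to show non-inferiority, or how quickly that chance falls if group support is a few points worse than one-to-one support.

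**Working it through.** **Inputs from the article.** k = 18 facilities per arm; between-cluster variance 0.1 on the logit scale, which agrees with the stated ICC: 0.1/(0.1 + π²/3) = 0.0295; rates 65% and 80%; margin 15%, read as percentage points with the individualized arm as reference; 95% interval.

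**Assumption.** The number of minimal requirements per facility, m, is not in the article (a supplement that is not shown may give it). I use m = 10 to 20 and one time point per facility.

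**1. The stated figures as a difference test (two-sided 0.025, z = 2.241), logit scale.**
Variance = 2 × 0.1/18 + [1/(p₁(1−p₁)) + 1/(p₂(1−p₂))]/(18m).
- 65% vs 80%, m = 13: 0.0111 + (4.396 + 6.25)/234 = 0.0566, SE 0.238. Logit difference 0.767. Φ(0.767/0.238 − 2.241) = 83.7%.
- 60% vs 80%, m = 13: variance 0.0111 + (4.167 + 6.25)/234 = 0.0556, SE 0.236. Logit difference 0.981. Power 97.2%.

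Both match 84% and 97%. At two-sided 0.05 the first becomes Φ(3.225 − 1.96) = 90%, so the alpha label alone is worth about 6 points.

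**2. The stated figures as a non-inferiority test with equal true rates (one-sided 0.025, z = 1.96), margins 15 and 20 points.**
- Logit scale, both arms 80%, limits 65% and 60%, m = 13: variance 2 × (0.1 + 1/(13 × 0.16))/18 = 0.0645, SE 0.254. Φ(0.767/0.254 − 1.96) = 85.6%; Φ(0.981/0.254 − 1.96) = 97.1%.
- Risk difference, both arms 65%: 82.6% and 97.1% at m = 12; 84.8% and 97.9% at m = 13.

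These also lie within about 2 points of 84% and 97%, so reproducing the figures does not separate the two readings.

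**3. Power of the planned test, margin 15 points, 18 per arm.**
Variance per arm = [p(1−p)/m + 0.1(p(1−p))²]/18; power = Φ((0.15 − deficit)/SE − 1.96).
Example, 80% vs 75%, m = 13: variances 0.000826 + 0.000997, SE 0.0427; Φ(0.10/0.0427 − 1.96) = 65%.

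| True fidelity (individualized vs collaborative) | m = 10 | m = 13 | m = 20 |
|---|---|---|---|
| 80% vs 80% | 91% | 96% | 99% |
| 65% vs 65% | 77% | 85% | 94% |
| 80% vs 75% | 56% | 65% | 79% |
| 80% vs 70% | 17% | 20% | 26% |
| 80% vs 65% | 2.5% | 2.5% | 2.5% |

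The last row is Φ(0 − 1.96) whatever m is. At 80% vs 60% and m = 13, SE is 0.0466 and power is Φ(−0.05/0.0466 − 1.96), about 0.1%. A cluster-level simulation (40,000 runs) at m = 10 and 13 agrees: 91.2% and 95.9% at equality (both arms 80%), 56.4% and 65.9% at a 5-point deficit, 2.9% and 3.0% at 15 points.

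**4. Loss.** 18/0.9 = 20 per arm. Correct.

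**The case against.** The strongest defence is that this may be a non-inferiority calculation described loosely. The 15-point gap equals the margin; 80% is the article's own threshold for high fidelity; 65% may be the non-inferiority limit for an 80% reference; and the 20% may be a wider margin, for which non-inferiority power does rise. The alpha may be a slip for 2.5% per tail. Step 2 shows that the figures allow this.

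That defence stands to this extent. A reader might infer that a superiority simulation was certainly run, but the numbers do not prove it; the point rests on the wording and on the alpha. A reader might also infer that the trial is underpowered. That is not shown either: with equal arms, power is about 77–99% over the range examined. The 2.5% at a 15-point deficit is what any non-inferiority test gives on its margin; it shows that the stated scenario cannot be the one in which success is expected, not that the sample is too small. Nor does the Discussion's remark about being slightly overpowered claim more than it should, since it concerns 40 facilities recruited against 36 needed, as cover for drop-outs.

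The defence does not remove the mismatch. The text never calls 65% a limit, gives no true rates at which non-inferiority is expected, and states an alpha that does not fit the interval. Nor is this detail left to a fuller document: the article gives a power basis, and as written it belongs to another test.

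**Conclusion.** The point holds as a mismatch in what is written. The stated power and alpha read as those of a difference test and do not match the primary non-inferiority rule, so power for that rule is not given. Which simulation was run cannot be settled from the article. The sample size is not shown to be wrong: it looks adequate if the two modes are truly equal and much less so if the collaborative mode is about 5 points worse. All magnitudes depend on the assumed m, on normal approximations and on one time point per facility. The 2.5% at the margin and the alpha conflict do not depend on m; the latter assumes that the 95% interval is two-sided.

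**What to change.** Restate the power for the planned rule:

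- margin of −15 percentage points against the individualized arm, lower limit of a two-sided 95% interval, one-sided alpha 0.025;
- the true fidelity assumed in each arm, and the number of minimal requirements per facility used in the simulation;
- power at a true difference of 0 and, as sensitivity, at a small deficit such as −5 points.

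Replace the wording about detecting a 15% difference and "a two-sided alpha of 0.025". If 65% was meant as the non-inferiority limit for an 80% reference, say so. If the simulation was done for a difference test, re-run it for the lower-limit rule; if it was already done for non-inferiority, rewording and the sensitivity case are enough.

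The cost is a change of text and at most a re-run of an existing simulation. Keep 40 facilities. Power at a small true deficit will look less favourable than 84%.
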